### Data collection and monitoring

2.8

During the screening period, participants will complete their sociodemographic characteristics collected by the questionnaire. Personal information and data collected during the screening period will be shared and managed by the hospital. The monitoring of data and research performances will be conducted regularly by researchers from the Cheonan Korean Medicine Hospital of Daejeon University (Cheonan, Republic of Korea). The final trial dataset will be accessible to statisticians and the principal investigator (PI).

### Statistical analysis

2.9

Statistical analysis will be primarily based on the principle of the full analysis set. Missing values will be analyzed by the last observation carried forward method. For each of the 2 devices, the VAS score and time at which the participant's pain disappears will be measured, and descriptive statistics will be presented as a mean, standard deviation, median, and minimum and maximum values. The analysis method for evaluation of the variables of efficacy will involve confirmation of the normality of the values and then comparison using the paired *t* test or Wilcoxon signed-rank test. The McNemar test will be used to analyze the VRS score, total number of nonbleeding cases, number of blood collection failures, number of cases of delayed hemostasis, and number of participants. The significance level will be set at *P* < .05 and the confidence interval at 95%. All statistical analyses will be performed using SPSS Statistics for Windows version 20.0 (IBM Corp, Armonk, NY).

If necessary, subgroup analyses of outcome variables, such as the demographic variables measured at baseline (e.g., sex, age, duration of illness, treatment expectation) can be performed. Safety assessments will be performed primarily by analyzing the frequency of adverse events and serious adverse events (SAEs) that researchers suspect to be related to treatment. The collected safety data will be summarized appropriately. All adverse events that occur will be listed with a detailed description. All SAEs will be recorded descriptively. The adverse events will be collected through patient symptom reporting and researcher observation. The frequency of each adverse event associated with or unrelated to the intervention will be recorded and analyzed using descriptive statistics. There is no intermediate analysis of this study, and the final decision regarding the completion of the clinical trial will be made by the PI.

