### Study design

2.1

This randomized, controlled, double-blind, matched-paired clinical trial will compare the pain associated with use of 1 bloodletting device (ROAH-L-NO1) to that associated with a control device (LANZO 1.5). One hundred outpatients will be recruited from the Daejeon University Cheonan Korean Medicine Hospital through advertisements posted on bulletin boards in hospitals. Recruitment commenced in October 2019, and the trial is expected to end in December 2019. One hundred patients who meet the eligibility criteria for this study will be randomly assigned to groups A, B, C, or D. The intervention will begin on the day of the screening visit. Depending on the study group, 2 procedures will be performed, 1 for each participant's hand, in the order of the right and left hand labeled on the bloodletting devices according to the randomization code. The total duration of the clinical trial will be 3 months.

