### Intervention

2.6

The test device (ROAH-L-NO1) will be manufactured by Roahmed Medical Device Co. (Changwon, Republic of Korea), and the control device (LANZO 1.5) will be manufactured by GMMC Medical Device Co (Seoul, Republic of Korea). Both devices will be applied to the participants’ 3rd finger.

All eligible participants will receive a treatment according to the allocated group, RTLC, LTRC, RCLT, or LCRT, on the day of the screening visit. To maintain the double-blinded nature of the study, during the procedure, a screen will be placed between the participant and the operator. The operator will use the test and control devices on the participants on the outside of the screen, and participants will be indistinguishable to which hand the test device is assigned. The operator will practice using the randomized device on the 3rd finger of 1 hand of the participant. If blood is collected to the extent that the blood glucose level can be measured, it will be determined to be successful, and the 1st measurement will be completed. If no blood is collected, the participant will be checked to confirm no bleeding (“nonbleeding”), and treatment will be applied again after 10 minutes to determine whether blood collection is successful. When the total number of instances of nonbleeding is 3, no further procedure will be recorded, and “blood collection failure” will be recorded. The operator will check the participants’ state of hemostasis after bleeding, and if hemostasis does not occur within 3 minutes (“delayed hemostasis”), the participant will be checked again for complete hemostasis. If hemostasis does not occur for more than 10 minutes, the operator will check the participant for hemostasis abnormalities, and the operator will stop the clinical trial and seek medical attention for the participant. The secondary measurement will be performed 10 minutes after the primary measurement in the same way on the same area of the participants’ opposite hand. Participants will undergo the intervention from 1 to 3 times only on the day of the procedure.

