### Outcome measures

2.7

The primary outcome will be the VAS score, which will be assessed upon successful blood collection. The secondary outcomes will be the verbal rating scale (VRS) score and the time at which pain disappears after blood collection (second), which will be assessed upon successful blood collection. In addition, the total number of nonbleeding cases, number of blood collection failures, number of cases of delayed hemostasis, and number of participants will be counted. Participants’ data will be anonymized and coded by a specific program.

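### Last observation carried forward has no valid value to carry in this one-score-per-device design; where it can be applied, it pulls the estimated device difference toward zero and narrows its confidence interval

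*Protocol article*

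**What the plan says.** Section 2.9 fixes the missing-data rule without limiting it by device, hand or outcome: "Missing values will be analyzed by the last observation carried forward method". The same section sets the population ("Statistical analysis will be primarily based on the principle of the full analysis set") and a within-person test ("comparison using the paired *t* test or Wilcoxon signed-rank test").

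The design leaves two scores per person:

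- Section 2.1 (Study design): "2 procedures will be performed, 1 for each participant's hand". By the allocation codes in section 2.5, the two hands always receive different devices.
- Section 2.6 (Intervention): "The secondary measurement will be performed 10 minutes after the primary measurement in the same way on the same area of the participants’ opposite hand".
- Section 2.7 (Outcome measures): "The primary outcome will be the VAS score, which will be assessed upon successful blood collection". Time until pain disappears is taken at the same point. An attempt without bleeding therefore leaves no score behind.
- Section 2.6, on repeated unsuccessful attempts: "When the total number of instances of nonbleeding is 3, no further procedure will be recorded, and “blood collection failure” will be recorded".

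No VAS before the first procedure is described. Section 2.3 removes a participant after three nonbleeding attempts on one finger. The article does not say whether such a person is imputed or dropped in the full analysis set.

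**The concern.** Carrying a value forward presupposes an earlier measurement of the same quantity under the same treatment. Here there is none. Two patterns of single missing scores are possible, and the rule fits neither:

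- **Second score missing.** The only earlier VAS is from the other device on the other hand. Carrying it forward makes the person's test-minus-control difference exactly 0, whatever the device does.
- **First score missing.** There is nothing to carry.

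Which device's score can be filled therefore depends on randomized order: a missing test-device score only in groups C and D, and a missing control score only in groups A and B.

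Missing scores are foreseeable. Section 2.4 allows 15% dropout, and sections 2.3 and 2.6 describe withdrawal, collection failure and stopping for delayed hemostasis. At stake are the size of the pain difference and its 95% confidence interval. Time until pain disappears is affected in the same way.

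**Working it through.** **Inputs.** From section 2.4: two-sided alpha 0.05 (sidedness is not printed, but two-sided reproduces the plan's figure), power 0.80, 15% dropout, 100 participants. Assumed: SD of the within-person difference set to 1 (none is given), true effect d = 0.305 in those units, and second scores missing at random in a share m.

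**The plan's own sample size.** For a 2 × 2 crossover, n per sequence = (z₀.₉₇₅ + z₀.₈₀)² / (2d²).

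- d = 0.61 ÷ 2 = 0.305 gives 42.19, so 43, as stated. Then 43 × 1.15 = 49.5, so 50 per group and 100 in total, as stated.
- The effect as printed, (0.61 ÷ 2) ÷ 3 = 0.102, gives 380. The printed division by 3 does not fit the stated 43, so 0.305 is used below as the value that does.

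**Effect of the rule.** A share m of the N differences becomes 0 and the rest keep mean d and SD 1:

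- mean = (1 − m)d
- variance = (1 − m) + m(1 − m)d²
- SE = √variance / √N, against 1/√(N(1 − m)) for the observed pairs.

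At m = 0.15: mean = 0.85 × 0.305 = 0.259; variance = 0.85 + 0.1275 × 0.0930 = 0.862; SD = 0.928; SE = 0.093. From 85 pairs, SE = 1/√85 = 0.108.

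| Second scores missing | Mean, carried forward (true 0.305) | SE, carried forward | SE, observed pairs | 95% CI coverage, carried forward |
|---|---|---|---|---|
| 2% | 0.299 | 0.099 | 0.101 | about 95% |
| 5% | 0.290 | 0.098 | 0.103 | about 95% |
| 15% | 0.259 | 0.093 | 0.108 | about 92% |

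Coverage is by simulation. At 15% missing (40,000 trials) it was 92.3% with carried values and 95.2% with complete pairs; mean interval widths were 0.367 and 0.430.

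**Effect on the test.** Mean and SE shrink almost together. At 15% missing the ratio of mean to SE is 2.79 with carried values and 2.81 with complete pairs. Simulated power is 79.4% either way, and type I error is 5.1% either way.

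**The case against.** Five points can be made in defence of the plan.

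1. *The article never says that a score crosses from one device to the other.* True. It could also be read as leaving nothing to carry, so that the pair drops out. But the stated rule is unrestricted, and the other device's score is the only earlier value available. On the milder reading the rule does nothing and should still go.

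2. *The smaller SE is not false precision in itself.* This stands. With 15% zeros inserted, the estimator's own sampling SD is √0.85 / 10 = 0.092, which the reported 0.093 matches. The coverage loss comes from the shift toward zero. It remains true that the interval is narrower than the 85 observed pairs support.

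3. *15% is an upper end.* This stands. Both procedures fall on one day, 10 minutes apart. Section 2.3 may remove collection failures before any imputation, and a missing first score cannot be filled at all. At 2% to 5% missing, coverage is practically intact.

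4. *The assumed effect matters.* This stands too. At the printed 0.102, coverage is 94.7% even at 15% missing. Effects of 0.61 SD or more would show far worse coverage, but section 2.4 expects this device to do less than the earlier one from which 0.61 was taken, so those are not planning scenarios.

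5. *A reader might infer damage to the McNemar comparisons.* The documents do not support that. McNemar's test uses discordant pairs only, so an extra concordant pair leaves it unchanged. Nonbleeding and collection failure are recorded events, not missing values.

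**Conclusion.** The point holds for the effect estimate and its 95% confidence interval, for VAS and for time until pain disappears. The stated rule either fills a score from the wrong device or cannot be applied. The estimated difference shrinks in proportion to the share of missing second scores: 2% at the low end shown and 15% at the high end, with coverage going from about 95% to about 92%.

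A reader might go further and infer that the trial risks a false-positive result or loses appreciable power. The calculations do not support this: relative to complete pairs, type I error and power are essentially unchanged, and the shift is toward no difference.

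The sizes rest on 100 participants, an SD of differences of 1, a true effect of 0.305 SD and scores missing at random. The proportional shrinkage of the mean does not depend on the SD or the effect; the coverage figures do. If leaving before the second hand depends on the pain felt, the size would differ. The direct consequence, a difference of exactly 0 for each filled pair, would not.

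**What to change.** Delete last observation carried forward for the device comparison in section 2.9 and analyse observed data only, in one of two ways:

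- complete pairs with the planned paired test; or
- a likelihood-based repeated-measures mixed model with device, period and hand as fixed effects and participant as random effect. It also uses participants with one score and fits the repeated-measures analysis that the Abstract names for primary efficacy.

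State that a VAS or pain-duration value is never imputed from the other device. Keep collection failure as its own recorded outcome, as section 2.7 already does, and say how participants removed under section 2.3 enter the full analysis set.

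The cost is analysis wording only. No added participants are needed for this change: the 100 already include the dropout allowance, and 85 complete pairs give 79.4% power at 0.305 SD, the same as with carried values.

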**Methods::**

This study will be a randomized, controlled, double-blind, and matched-paired-designed clinical trial. Four groups, RTLC, LTRC, RCLT, and LCRT (T = test device, C = control device, L = left, R = right), will be randomly allocated. Total duration of the clinical trial will be 3 months. The subjects will be performed from 1 to 3 times only on the day of the procedure. The primary outcomes will be measured using pain visual analog scale score and the secondary outcomes will include verbal rating scale and the time at which the pain disappears after blood collection (second), the total number of “nonbleeding” cases and subjects, the number of “blood collection failure” and subjects, the presence of “delayed hemostasis,” and the number of subjects. Repeated-measure analysis will be used to measure primary efficacy based on full analysis set.

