**Table 2 T2:**

Estimated magnitude of Buzzy effect on pain reduction.

Because the present study will proceed to the point of blood collection, not only the pain intensity is weaker than the previous study, but the duration and intensity of vibration are shorter or weaker than that of Buzzy effect. Therefore, the effect size on the pain reduction of the test device is thought to be smaller than that of Buzzy effect. In the design of the clinical trial, 4 sequences will be assigned, but since the 2 treatments and 2 periods are basically 2 × 2 cross designs, the formula for calculating the sample size corresponding to the design will be applied mutatis mutandis. Assuming that the effect size of the study device is n = (0.61 ÷ 2) ÷ 3,” the sample size (class 1 error *a* = 0.05; power 1 − *b* = 0.8) to be assigned to each device sequence will be as follows: 

Forty-three participants will be required for each treatment group. In addition, considering a 15% dropout rate, the number of participants required per treatment group will be 50. One hundred participants will be calculated as the total number of participants in this study.

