### Randomization and blinding procedures

2.5

There will be 4 assignments according to the order of the bloodletting devices (T = test device, C = control device) and blood collection location (L = left, R = right): RTLC (group A), LTRC (group B), RCLT (group C), and LCRT (group D). Balanced block randomization will be used to evenly assign the participants to each group. The process will be as follows:

1.number the assignment for each group (A = group A, B = group B, C = group C, D = group D),2.randomly select 1 block size among 4, 8, 12, and 16,3.randomly select 1 sequence that can be allocated to 4 groups evenly for each block size,4.assign participants to the selected sequence, and5.repeat steps 2 to 4 for 100 participants.

Participants who meet all registration criteria will be randomly assigned to a randomization identification code (e.g., BCU-R-001, BCU-R-002, …, BCU-R-036) in the order generated by a computer randomized program. The randomization identification code indicates the type of bloodletting device and the order of the left and right hands. Additionally, the participants and the assessors who will be collecting the data will be blinded to the group allocation.

Information of the intervention assignment will be stored in the 3rd statistical department. The randomization code will be placed in an opaque envelope and stored in the hospital. With the exception of disclosure to individual patients in emergency situations, randomization, and blinding will not be disclosed to researchers until the end of the trial.

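### The abstract and section 2.9 name different analyses for the primary VAS, section 2.9 lets a normality check choose the test, and neither test it names uses the randomised order and hand factors

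*Protocol article*

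**What the plan says.** - **Abstract, Methods:** "Repeated-measure analysis will be used to measure primary efficacy based on full analysis set".
- **Section 2.9, Statistical analysis:** the efficacy variables go through "confirmation of the normality of the values and then comparison using the paired" *t* "test or Wilcoxon signed-rank test". Repeated-measures analysis is not mentioned, and neither is period, hand or sequence.
- **Section 2.7, Outcome measures:** "The primary outcome will be the VAS score, which will be assessed upon successful blood collection". The VAS is therefore among the efficacy variables covered by section 2.9.
- **Section 2.5, Randomization and blinding procedures:** "There will be 4 assignments according to the order of the bloodletting devices" and the hand used, giving RTLC, LTRC, RCLT and LCRT. Allocation is even: "Balanced block randomization will be used to evenly assign the participants to each group".
- **Section 2.4, Sample size calculation:** the crossover formula is borrowed "since the 2 treatments and 2 periods are basically 2 × 2 cross designs".
- **Section 2.6, Intervention:** the two punctures are consecutive. "The secondary measurement will be performed 10 minutes after the primary measurement in the same way on the same area" of the other hand.

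**The concern.** There are two linked problems.

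**The primary test is not single.** The abstract and the methods label the primary analysis differently, and the methods version branches on the observed data. One branch compares means and the other compares ranks, so the reported effect measure is also open until the data are seen.

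**The analysis does not follow the design.** Order and hand are built into the randomisation so that they can be separated from the device effect. A one-sample test on the within-person differences puts any first-versus-second or right-versus-left difference back into the error term. The trial is sized for about 80% power with no allowance for this, so any such difference comes off the planned power and widens the confidence interval.

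**Working it through.** **1. The plan's own sample size.** For a 2 × 2 crossover with two-sided alpha 0.05 (sidedness is not stated, so this is assumed) and power 0.80:

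n per sequence = (1.960 + 0.842)² / (2 × ES²)

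With ES = 0.61 ÷ 2 = 0.305 this is 7.849 / 0.186 = 42.2, rounded up to 43, as stated. The printed expression has a further ÷ 3, which would give 380 per sequence. That is a separate matter. Here 0.305 is used because it reproduces 43 under the design the text names. Two device orders × 43 = 86 participants. The nearest number above it that divides evenly over four sequences is 88, or 22 each.

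**2. Model for the within-person difference** (test minus control, in units of its SD after order and hand are removed):

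D = δ + s₁p + s₂h + e, with e ~ N(0, 1)

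- δ = 0.305 is the device effect.
- p is the order effect; s₁ = +1 if the test device comes first, −1 if second.
- h is the hand effect; s₂ = +1 if the test device is on the right, −1 if on the left.

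The document gives neither p nor h, so the values below are assumptions.

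**3. Bias.** Over four equal sequences s₁ and s₂ each average zero, so the mean of D estimates δ. Simulated means were 0.304 to 0.307 for a true 0.305. If completers are unequal, the bias is p × (test-first minus test-second) / N. A surplus of 4 among 86 at p = 0.5 gives 0.5 × 4/86 = 0.023 SD, against a device effect of 0.305.

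**4. Power and type I error.** For the paired t test, the mean of D has variance 1/N. The sum of squares about that mean is noncentral chi-square with N − 1 df and noncentrality N(p² + h²). The estimate is as precise as before, but its standard error is overstated by about √(1 + p² + h²). The model with order and hand terms uses noncentral t with N − 3 df. For N = 88:

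| Order p | Hand h | Paired t power | Adjusted power | Paired t type I error | CI width ratio |
|---|---|---|---|---|---|
| 0 | 0 | 80.8% | 80.8% | 5.0% | 1.00 |
| 0.3 | 0 | 78.3% | 80.8% | 4.1% | 1.04 |
| 0.5 | 0 | 73.7% | 80.8% | 2.9% | 1.12 |
| 0.5 | 0.3 | 71.1% | 80.8% | 2.3% | 1.16 |

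Simulation of four balanced sequences agrees to within about one percentage point. At N = 86 with no order or hand effects, the paired t test has 79.9% power and the adjusted model 79.8%, so adjustment costs under 0.1 point.

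**5. Does the branch matter?** In simulations with 88 pairs and a device effect of 0.305 SD, the paired t and Wilcoxon tests disagreed on significance in about 5% of trials when differences were normal. With heavy-tailed differences (t with 3 df, an assumption) they disagreed in about 13%.

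**The case against.** **The two labels may mean the same thing.** With two measurements per person, a one-factor repeated-measures ANOVA is the paired t test (F = t²). This stands, and it narrows the conflict to the Wilcoxon branch and the absent order and hand terms.

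**The rule is written in advance, and its type I error is sound.** This also stands. A Shapiro–Wilk gate at 0.05 followed by the t or Wilcoxon test, with 86 null differences (normal, or the difference of two gamma variables), rejected in about 5% of simulated trials. What remains is that the effect being estimated changes with the branch taken.

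**The power loss rests on assumed effects.** It does. An order effect as large as the whole device effect costs 2 to 3 points, and a loss of 7 points needs one about 1.6 times the device effect. The document offers no evidence for either.

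Two stronger readings are tempting, and the text does not support them:

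- *A reader might infer that leaving out order and hand biases the device comparison or inflates false positives.* Even block allocation cancels both effects in the mean. A modest imbalance among completers moves the estimate by about 0.02 SD, and the paired t test then rejects too rarely, not too often.
- *A reader might infer that normality is to be checked on the raw scores and not on the differences.* Section 2.9 speaks loosely of values, immediately before naming a paired test. The paired differences are a fair reading, and the details of the check can be left to an analysis plan.

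**Conclusion.** The point holds at the level of should-fix. The abstract and section 2.9 do not name the same primary analysis. Section 2.9 makes the choice between a mean and a rank comparison depend on the data, and neither of its tests uses the factors that define the four sequences. The harm is lost power and over-wide intervals. It is nil if order and hand have no effect, and about 2 to 10 percentage points over the range examined. Those figures assume a device effect of 0.305 SD of the difference, 88 evenly allocated completers, normal errors, and order and hand effects that the document does not supply. A significant result from the paired t test would remain valid.

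**What to change.** Name one primary analysis, in the same words, in the abstract and section 2.9: a linear mixed model for VAS with fixed effects for device, period and hand and a random participant effect. With complete pairs this is equivalent to regressing the within-person difference on order and hand. Report the adjusted mean difference with its 95% confidence interval.

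Remove the normality check as the means of choosing the primary test. Keep the paired t and Wilcoxon signed-rank tests, both on the paired differences, as sensitivity analyses.

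The cost is a few sentences of wording, one additional model, and two degrees of freedom. Sample size, randomisation and data collection do not change.

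### McNemar's test, a test for paired yes/no data, is assigned to the VRS score and to the total count of nonbleeding cases, and fits neither secondary outcome as defined

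*Protocol article*

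**What the plan says.** Section 2.9 of the protocol article (Statistical analysis) names two families of test. After describing how the VAS score and the time to disappearance of pain will be summarised, it plans, subject to a normality check, a "comparison using the paired *t* test or Wilcoxon signed-rank test". The next sentence reads: "The McNemar test will be used to analyze the VRS score, total number of nonbleeding cases, number of blood collection failures". Delayed hemostasis and numbers of participants complete that list.

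The outcomes are described elsewhere:

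- **VRS.** Section 2.7 (Outcome measures): "The secondary outcomes will be the verbal rating scale (VRS) score and the time at which pain disappears after blood collection". It is taken when collection succeeds. The article gives no number of levels and no threshold that would make it yes/no.
- **Nonbleeding.** Section 2.6 (Intervention): after a nonbleeding attempt, "treatment will be applied again after 10 minutes to determine whether blood collection is successful". The upper limit is also given there: "When the total number of instances of nonbleeding is 3, no further procedure will be recorded, and “blood collection failure” will be recorded".
- **Delayed hemostasis.** The abstract treats this as present or absent: "the presence of “delayed hemostasis,” and the number of subjects".

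Section 2.3 (Withdrawal and dropout) adds that a participant with three nonbleedings on the same finger is excluded from the study.

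**The concern.** McNemar's test compares the two discordant cells of a paired 2 × 2 table. Here each participant has to supply one yes/no result for the test device and one for the control device. A score with several ordered levels, or a count from 0 to 3, does not form that table until someone decides how to collapse it, and the article gives no rule for doing so.

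The VRS is one of two secondary outcomes that describe the pain itself. If its analysis depends on a threshold that is not fixed, its result depends on that choice. Even a well-chosen threshold discards most of the ordering that the scale records. For nonbleeding, the article does not say whether the unit of analysis is the event or the participant, and the test suits only the second.

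This is not a detail left to an analysis plan. The article names a specific test for specific outcomes, and for two of them the pairing does not fit.

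**Working it through.** **Step 1: data type against test.** McNemar needs one binary value per device per participant.

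| Outcome in the McNemar sentence | Form according to the article | Fits McNemar? |
|---|---|---|
| VRS score | Score, no cut-off stated (2.7) | No, unless dichotomised |
| Total nonbleeding cases | Repeatable event, 0 to 3 per hand (2.6) | No, as a count |
| Blood collection failure | Three nonbleedings reached or not (2.6) | Yes |
| Delayed hemostasis | Present or absent (abstract, 2.6) | Yes |
| Participants with an event | Yes/no per device | Yes |

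An example for nonbleeding: a participant with two nonbleedings on one hand and one on the other has a count difference of 2 − 1 = 1. Coded as any nonbleeding, the pair is yes/yes, which is concordant and contributes nothing to McNemar.

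**Step 2: inputs for an illustration on the VRS.** The article gives no power figure for the VRS, so there is none to reproduce. Two inputs are borrowed from section 2.4:

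- *Shift.* 0.61 ÷ 2 = 0.305. This value reproduces the article's 43 per group: (1.960 + 0.842)² ÷ (2 × 0.305²) = 42.19, rounded up to 43. The further division by 3 printed there would give 380; that is a separate matter. Using 0.305 as a shift in SD units on a latent pain scale is my assumption.
- *Pairs.* 100 × (1 − 0.15) = 85, after the stated 15% dropout; 100 pairs were also run.

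The article gives neither the number of VRS levels, nor the category boundaries, nor the within-person correlation. I assumed 5 levels and correlation 0.5, then varied both. Tests are two-sided at 0.05.

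**Step 3: model.** Each participant has two normal latent values with the stated correlation, one shifted by 0.305, and both are cut at the same four points. The signed-rank test uses the difference in category. Exact McNemar uses the scale split at each boundary in turn, with a binomial test of the discordant pairs against 0.5. The symmetry extension (McNemar–Bowker) sums (n_ij − n_ji)² ÷ (n_ij + n_ji) over all pairs of categories.

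**Step 4: power.**

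| Setting (correlation 0.5) | Signed-rank | Exact McNemar at the four cut-points | Symmetry test |
|---|---|---|---|
| 85 pairs; boundaries −1.2, −0.3, 0.5, 1.3; 3,000 runs | 0.72 | 0.25, 0.40, 0.33, 0.12 | – |
| 100 pairs; boundaries −0.8, 0.2, 1.0, 1.8; 1,500 runs | 0.78 | 0.38, 0.47, 0.26, 0.03 | 0.33 |

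The simulation error is small: √(0.40 × 0.60 ÷ 3,000) ≈ 0.009 in the first row.

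**Step 5: other assumptions.**

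- 85 pairs, 4 or 5 levels, correlation 0.5: signed-rank 68–70%, McNemar 4–41%, symmetry test 22–34%.
- 4 or 5 levels, correlation 0.7, 85 and 100 pairs: signed-rank 85–95%, McNemar at most 59%, symmetry test at most 60%.
- 3 levels, 85 pairs: signed-rank 62%, McNemar 25–42%.

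**Step 6: no device effect.** With 100 pairs the rejection rates were 0.044 (signed-rank), 0.022 (symmetry test) and 0.013 to 0.032 (McNemar at the four cut-points). With 85 pairs and 3 to 5 levels, McNemar and the symmetry test gave 0.02 to 0.04. A cut-point fixed in advance does not raise the false-positive rate.

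**The case against.** Several points on the other side stand.

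- **The test is not invalid in the sense of excess false positives.** A reader might infer that it is. Step 6 shows that a prespecified dichotomy and the symmetry extension both hold the 5% level. The loss is in power and in dependence on the cut-point. Nor does the article say that a threshold would be chosen after seeing the data; it says nothing about a threshold.
- **The article does not treat each nonbleeding attempt as a pair.** A reader might infer this and expect wrong standard errors. The design pairs the two hands of a participant, and the abstract lists cases and subjects side by side. Counting participants with any nonbleeding per device is a proper use of McNemar. What remains is that the total number of cases, which is also listed, is a count and does not fit.
- **Much of the sentence is right.** Collection failure, delayed hemostasis and participants with an event suit McNemar.
- **The power figures are illustrative.** They rest on a scale the article does not describe. With fewer levels the gap narrows, and with only two levels McNemar would be the natural test.
- **The VRS is not called a key outcome.** Section 2.7 lists it beside time to pain disappearance with no ranking.

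None of this supplies a cut-off for the VRS or turns a count of up to three into a yes/no value.

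**Conclusion.** The concern holds for two secondary outcomes, the VRS score and the total number of nonbleeding cases: the test named in section 2.9 does not match the form in which they are recorded. For the VRS, the consequence is lost power and a result that depends on an unstated threshold. Under the assumed 5-level scale, correlation 0.5, shift of 0.305 SD and 85 pairs, power is about 70% for signed-rank against about 12% to 40% for exact McNemar. The size of the gap depends on those assumptions; its direction held in every multi-level setting tried. No magnitude is claimed for nonbleeding, because the article gives no expected rates.

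I grade this should-fix. The documents do not support a claim of inflated type I error, and they do not show that the rest of the McNemar sentence is wrong. The primary VAS comparison and the sample size do not depend on it.

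**What to change.** Reword the McNemar sentence in section 2.9 so that each outcome has a test suited to its form:

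1. **VRS.** Wilcoxon signed-rank test on within-participant differences, or a paired ordinal model. State the number of levels.
2. **Nonbleeding count per hand (0 to 3).** Wilcoxon signed-rank test among participants with both hands attempted.
3. **Any nonbleeding, collection failure and delayed hemostasis.** Exact McNemar, each coded yes/no per participant and device.
4. **Incomplete pairs.** State how a participant excluded under section 2.3 after failure on the first hand enters these comparisons. The second hand may then be unmeasured, so neither a count difference nor a McNemar pair exists for that person. Likewise, the VRS is taken only on success, so a VRS pair needs both hands to succeed.

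The cost is a few sentences. Data collection and the number of participants do not change, and the signed-rank test is already named in the same section. The change should be made before the data are unblinded.
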